#### Ascertainment of hand dermatitis and description of the photographic method

The protocol for photographing hands and wrists has been developed in consultation with a medical photographer and is consistent with the views required for the photographic assessment scale described by Coenraads [39]. It prescribes a method for obtaining repeatable standardised digital images that allow assessment of skin condition and colour.

As a last resort, where the local field worker is unable to make personal contact with a participant at follow-up, they will be offered an opportunity to send the SCIN research team ‘selfie’ photographs of their hands and wrists.

Initial assessment of photographs will be carried out by a dermatology research nurse (blind to intervention group), who will classify them as showing ‘definite/possible dermatitis’ or ‘no dermatitis’. All images classed as ‘definite/possible dermatitis’, together with a sample of 250 that are classed as ‘no dermatitis’ will then be assessed independently by two dermatologists. Final determination of whether or not dermatitis is present will be according to the opinion of the dermatologists, with any differences between them resolved by discussion. Provided the dermatologists do not identify a significant rate of dermatitis among the images that the nurse originally classed as ‘no dermatitis’, her assessment of ‘no dermatitis’ will be accepted for the images that were not selected for dermatologist assessment.

Our rationale for ascertaining any, and not only more severe hand dermatitis, is that even minimal hand dermatitis progresses to significant hand eczema in a cumulative way over time [39]. However, the dermatologists will also grade disease severity since severe hand dermatitis causes more distress and is associated with greater loss of time from work. We will use a method developed by Coenraads et al. [39] for classifying hand eczema severity: a simple categorization into five grades (clear, almost clear, mild, moderate, severe and very severe). Again, differences between the two dermatologists will be resolved by discussion.

### Data analysis

Outcomes will be assessed separately for the two study groups (student nurses and ICU nurses).

#### Outcome measures

For each study group, the principal outcome measure will be the difference between intervention-plus and intervention-light sites in the change in point prevalence of visible hand dermatitis from baseline to the end of follow-up.

Secondary outcomes will be the difference between intervention and control sites in:The difference between intervention and control sites in the change in prevalence and severity of visible hand dermatitis from baseline to the end of follow-up (as ascertained by the dermatologists)Days lost from sickness absence and days of modified duties because of hand dermatitis per 100 days of nurse time during the 12 months of follow-upThe change from baseline to after completion of the BCP, and to the end of the 12-month follow-up in beliefs about dermatitis prevention behavioursThe change from baseline to the end of follow-up in the reported frequency of: use of hand rubs for hand cleansing; hand-washing with water; and use of moisturising creams (for student nurses, who will not have started clinical attachments at the beginning of the study, this will reduce to differences between the intervention and control sites at the end of the follow-up)The change from baseline to the end of follow-up in quality of life scoreThe use of moisturiser provided for the intervention (in terms of requests for further supplies by student nurses and orders for supplies of moisturisers by ICUs)

We will also document the reported participation in the BCP, reasons given for not participating, and comments on its content.

### Method of analysis

Differences in changes in the prevalence of the primary and secondary outcomes from baseline to follow-up between the two arms will be assessed by random-intercept multi-level models to account for possible clustering by site. For the primary outcome, the relative odds of having dermatitis at follow-up in the intervention-plus group as compared to the intervention-light group after adjusting for dermatitis at baseline will be estimated using a random-intercept logistic regression model. If inadvertent potentially confounding changes occur at some sites during the course of the study, we will carry out sensitivity analyses excluding the sites concerned. We will test whether differences between the intervention and control groups in dermatitis prevention behaviours are mediated by differences in beliefs and plans about the relevant behaviour.

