### Sampling

We identified all NHS sites in the UK that train nurses, have an in-house OH service, and have at least one ICU. We first wrote to the lead occupational physician in each eligible site in December 2011, asking their willingness, in principle, to collaborate in a trial; and we wrote again in May 2012 and January 2014 asking them to confirm their willingness to collaborate. We also invited additional sites to sign up to the study via national OH newsletters. This included some sites that had an ICU but did not train nurses, and vice versa. In order to avoid the risk of student nurses moving placements from an intervention to a control site (or vice versa) during the study period, we generally invited only one site in each city or town to participate in the study. The exceptions were London and Manchester. In London, three sites were identified in which student nurses did not move to neighbouring sites during their training. In Manchester, we identified sites where students at three local universities undertake their clinical placements during their first year of nursing training, and ensured that these sites were clustered appropriately to prevent cross-contamination in the study.

A summary of the number of participating sites is provided below:12 sites recruiting both ICU nurses and student nurses (NHS trusts/health boards)18 sites recruiting ICU nurses only (NHS trusts/health boards)5 sites recruiting student nurses only (university-based OH departments)

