### Randomisation

Randomisation will be carried out using fixed blocks of two, stratified by small or large site with or without student nurses. Two sites will be randomised at a time and the King’s Clinical Trials Unit will control the order of the randomisation in order to ensure allocation concealment. Baseline will be collected prior to randomisation.

For the purpose of analyses by intention-to-treat, the date of entry into the study for each participant will be date when they sign the consent form. Although student nurses can only contribute useful information if they progress to clinical work, in practice very few fail to do so once they have begun their nursing studies.

Members of the study team will be notified of the outcome of randomisation in a blinded or unblinded manner, according to their role in the trial. The trial statistician (GN), methodologist (DC), and the dermatologists (HW, JE) will remain blinded to treatment allocation until after the primary analysis.

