### Sample size

Field workers will be encouraged to recruit as many eligible student nurses and ICU nurses as possible, with the aim of recruiting at least 40 student nurses and 40 nurses from the ICUs at each site.

To give an indication of power, we assumed that at the end of follow-up the expected prevalence rates overall at the intervention-light sites would be 24 % in both student and ICU nurses, that the intraclass correlation coefficient (ICC) is 0.05 (this corresponds to a variance inflation factor of 2.05 for student nurses and 2.8 for ICU nurses), and that 20 % of participants will be lost to follow-up. With a 5 % level of statistical significance (two-sided), we would have approximately 83 % power to detect a reduction in prevalence of dermatitis at follow-up in the intervention-plus sites to 10 % in student nurses and 91 % power to detect a reduction in prevalence to 10 % at follow-up in ICU nurses. For final prevalence rates of 12 %, the powers would be 68 % for student nurses and 78 % for ICU nurses, while for final prevalence rates of 14 %, the corresponding powers would be 51 % and 61 % respectively. The power will be higher if the ICC is lower than 0.05. (These calculations were carried out using the clustersampsi command in Stata v12.1 for difference in proportions.)

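### The stated primary model omits the factors by which sites were stratified, so its standard error is too wide to the extent that those factors predict dermatitis

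*Protocol article*

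**What the plan says.** The Randomisation section allocates sites, two at a time: "Randomisation will be carried out using fixed blocks of two, stratified by small or large site with or without student nurses".

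The Method of analysis section then describes "random-intercept multi-level models to account for possible clustering by site". For the primary outcome it says that the relative odds of dermatitis at follow-up "after adjusting for dermatitis at baseline will be estimated using a random-intercept logistic regression model". The abstract describes the analysis in the same terms: multi-level regression by site, adjusted for baseline values. The article nowhere places the stratification factors in a model. It also does not say that they are excluded or that the covariate list is complete.

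Under Data analysis, the two nurse groups are analysed separately. From the site counts under Sampling (12 sites with both groups, 18 with ICU nurses only, 5 with student nurses only), the student analysis has 12 + 5 = 17 sites and the ICU analysis has 12 + 18 = 30.

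**The concern.** Stratified blocking forces the arms to be balanced on site size and site type, so differences between strata largely drop out of the treatment comparison. A model without the strata cannot see this. Both factors are properties of the site, so any effect they have on prevalence is absorbed into the random-intercept variance, and the standard error of the treatment effect is computed as if that variation could still have fallen unevenly between arms. The model then reports less precision than the design delivered.

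In a trial with 17 and 30 clusters, between-site variance is a large part of the total. The protocol's own power for student nurses is 68 % at a follow-up prevalence of 12 % and 51 % at 14 %, so a standard error wider than necessary is worth avoiding.

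**Working it through.** **Which factors can matter in each analysis.** All 17 student sites have student nurses, so with/without student nurses is constant there and only site size can be omitted. Among the 30 ICU sites, 12 have student nurses and 18 do not, so both factors vary.

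**The protocol's own figures.** The Sample size section uses a two-proportion cluster formula with ICC 0.05. The stated variance inflation factors imply the cluster sizes: 1 + (22 − 1) × 0.05 = 2.05 for students and 1 + (37 − 1) × 0.05 = 2.8 for ICU nurses. The formula carries the full ICC and takes no credit for stratification. With 17 sites the effective number per arm is 8.5 × 22 / 2.05 = 91.2. A pooled normal test then gives 71.5 / 56 / 40.5 % power for 24 % against 10 / 12 / 14 %, not the stated 83 / 68 / 51 %. With 15 × 37 / 2.8 = 198.2 per arm, ICU power is 96 / 88 / 72 % against the stated 91 / 78 / 61 %. That these figures do not reproduce is a separate matter and does not bear on this point.

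**Simulation of the planned model, student nurses.** Inputs:
- 17 sites of 22 nurses, in two size strata of 9 and 8 (the split is assumed), allocated in blocks of two within stratum.
- Between-site variance on the logit scale 0.05 / (0.24 × 0.76) = 0.274, from the protocol's ICC and control prevalence.
- Baseline prevalence 20 % and a baseline log odds ratio of 1.2 (both assumed). Baseline dermatitis is drawn independently of stratum.
- Treatment log odds ratio 0 or −0.85. Since exp(−0.85) = 0.427, a control prevalence of 24 % becomes about 12 %: 0.316 × 0.427 = 0.135, and 0.135 / 1.135 = 0.119.
- v, the share of between-site variance explained by the stratum. The protocol gives no value, so 0, 25 % and 50 % were used.

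Each of 400 data sets per setting was analysed by random-intercept logistic regression with baseline dermatitis, without and with the stratum term (Wald test at 1.96). The first four result columns are under no treatment effect.

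| v | Without: model SE / empirical SD | With: model SE / empirical SD | Rejection without | Rejection with | Power without | Power with |
|---|---|---|---|---|---|---|
| 0 | 0.338 / 0.332 = 1.02 | 0.326 / 0.332 = 0.98 | 6.5 % | 7.2 % | 66.5 % | 68.5 % |
| 25 % | 0.338 / 0.323 = 1.05 | 0.307 / 0.322 = 0.95 | 4.8 % | 6.8 % | 67.2 % | 74.2 % |
| 50 % | 0.343 / 0.309 = 1.11 | 0.291 / 0.305 = 0.95 | 3.5 % | 6.2 % | 67.5 % | 76.0 % |

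The Monte Carlo standard error is about √(0.7 × 0.3 / 400) = 2.3 points for power and √(0.05 × 0.95 / 400) = 1.1 points for the null rejection rate.

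Two things follow. First, the empirical SD hardly changes when the stratum is added (0.309 and 0.305 at v = 50 %). The estimate was already about as precise as the design allows; it is the reported standard error that is wrong. Second, the with-stratum model's Wald standard error is 2 to 5 % too small at this number of sites, so part of the power difference comes from a slightly liberal test.

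**ICU nurses.** Only a site-summary analysis was run (30 sites, 24 % against 12 %). Power without and with stratum terms was 86 % and 86 % at v = 0, 88 % and 88 % at 10 %, 87 % and 90 % at 25 %, and 89 % and 96 % at 50 %. In the site-summary and mixed-model runs together, the type I error without stratum terms at v = 50 % was 2 to 3.5 %.

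**The case against.** The strongest objection is that this is a condensed article without its statistical analysis plan, and that a covariate list is the kind of detail such a plan supplies. The sentence on the primary model does not claim to be exhaustive, and it does not contradict the Randomisation section. That much stands: the plan may already contain these terms, in which case one sentence settles the matter. But the article is not silent on adjustment. It names the model, the random effect and one covariate, and an analyst who followed it as written would leave out the design factors.

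It can also be objected that the harm is conditional. This stands in full. The protocol assumes the same control prevalence in both nurse groups and one ICC, and says nothing about whether site size or type is related to dermatitis. If it is not, nothing material is lost.

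Two stronger readings are tempting. A reader might infer that the trial will fall short of its stated power because the strata are omitted. It will not for this reason, because the stated figures already assume the full ICC and no stratum adjustment. A reader might also take a larger effect from a site-level t analysis, which at v = 50 % and an odds ratio of 0.35 gives a standard error 15 to 19 % too wide and power of 69 % against 80 %. That is not the planned analysis; the planned model gives about 11 %.

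**Conclusion.** The point holds in a conditional form. As described, the primary model does not reflect the stratified allocation. To the extent that site size, or for ICU nurses the presence of student nurses, predicts dermatitis, its intervals are too wide and its test is conservative. The omission does not bias the comparison or inflate the type I error.

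For the 17-site student analysis the excess in the standard error is about 11 % if the strata explain half of the between-site variance, about 5 % if a quarter, and negligible if none. The power differences (8.5, 7 and 2 points) are upper guides, since part of each reflects the Wald test with few sites. These results rest on the assumed shares, stratum sizes and baseline effect, and on 400 runs per setting. The ICU result was not checked with the planned model. This is an inexpensive improvement that should be made, not a threat to validity.

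**What to change.** In Method of analysis, state that the student-nurse model includes site size (small/large) as a fixed effect, and that the ICU-nurse model includes site size and with/without student nurses. Apply this to the primary and secondary outcomes and fix it before unblinding. The Randomisation section keeps the trial statistician blinded until after the primary analysis, so the change can be made without suspicion of being data-driven.

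State also that the treatment effect will be tested against a small-sample, t-based reference on site-level degrees of freedom, because with 17 sites the adjusted Wald standard error tends to be too small.

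The cost is one site-level degree of freedom for students (17 − 2 = 15 falls to 17 − 3 = 14; critical value 2.131 to 2.145) and two for ICU nurses (30 − 2 = 28 falls to 30 − 4 = 26; 2.048 to 2.056). That is under 1 % on the interval width in either group. If the analysis plan already contains these terms, a sentence saying so is enough.

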### Economic analysis

In addition to analyses of clinical effectiveness, we will assess the cost-effectiveness of the interventions in the two staff groups from a healthcare and societal perspective. Healthcare costs will be calculated for the 12-month follow-up period and will be based on the number of contacts with clinical staff (occupational health, primary care staff, dermatologists, etc.) as a result of hand dermatitis, combined with appropriate unit cost information [40] and the cost of supplying moisturising creams (with costs obtained from the *British National Formulary* (*BNF*) for prescribed formulations). The service use information will be collected using a short self-report schedule based on the Client Service Receipt Inventory. These service costs will be added to the cost of the BCP itself, which will be based on development time and staff time accessing the package. Societal costs will be calculated by adding healthcare costs to the costs of lost production, based on days off work combined with wage rates. Cost comparisons between the groups will be made using bootstrapped regression models assuming that the cost data are skewed. Costs from both perspectives will be combined with the primary outcome measure in a cost-effectiveness analysis. If costs are reduced for one group and outcomes are better then it will be ‘dominant’. If one group has higher costs and better outcomes then incremental cost-effectiveness ratios (ICERs) will be generated, defined as the difference in costs divided by the difference in outcomes. Using the primary outcome measure, the ICER will indicate the extra cost incurred for one extra participant to be free of visible hand dermatitis in either hand at 12-month follow-up. There will be uncertainty around the cost and effectiveness estimates and this will be addressed using cost-effectiveness planes generated through repeated resampling from the data set to generate 1000 cost-outcome combinations and plotting these. To inform healthcare spending decisions it is helpful also to combine costs with quality-adjusted life years (QALYs). The most widely used QALY measure in England is the EQ-5D, which has been recommended for dermatological interventions [36]. This measure will be used at baseline and follow-up, and area under the curve methods used to produce QALYs. Similar analyses to those described above will be conducted to assess the relationship between costs and QALYs, but we will also generate cost-effectiveness acceptability curves (CEACs) to show the probability that the intervention is cost-effective for different threshold values placed on a QALY [41]. CEACs will still be produced but will be more exploratory; they will be used to identify threshold values where the likelihood of the intervention being cost-effective is 50 %, 60 %, 70 %, 80 % and 90 %). While standard unit costs are being used for most services it will be necessary to calculate the intervention costs specifically for the study. This will be based on estimates of staff time spent developing the intervention and staff time spent accessing it. We will increase/decrease both of these aspects in sensitivity analyses by 10–50 % to see the impact that these changes have on the probability that the intervention is cost-effective at the £20,000 and £30,000 QALY thresholds. Sensitivity analyses will also be conducted on the societal cost-effectiveness estimates by increasing/decreasing the cost of lost work time by 10–50 % and assessing the impact on the CEACs.

If the intervention is shown to be cost-effective then we will make estimates of the number of nurses who might access the intervention were it to become recommended practice. This will in turn allow us to estimate the budget impact for the NHS and the benefits in terms of total QALYs gained. Uncertainty around these estimates will be investigated through the sensitivity analyses describe above.

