### Intervention-plus

The intervention-plus in both staff groups will centre on a bespoke online behavioural change package (BCP) which will include advice: on when and when not to use gloves; on when to use antibacterial hand rubs; on when to use moisturising cream; and to contact OH early if hand dermatitis occurs.

The BCP has been developed by members of the study team with expertise in dermatology, occupational medicine, nursing, and health psychology. Care has been taken to ensure compatibility with current guidance on infection control. We have emphasised WHO recommendations that hands should only be washed with soap and water if visibly soiled. At all other times, hands should be cleansed with antibacterial hand rubs [8].

To maximise the probability of participants following best practice, they will be asked to form implementation intentions for performing each of the behaviours in their workplace. A record of each participant’s implementation intentions will be generated by the online BCP programme and emailed to them. In the event of a participant being unable to access the online BCP, they will be posted a paper-based magazine version of the BCP which will reflect the information provided in the online BCP. Participants will asked to read through the material provided and write down their action plans in spaces provided. They will then be asked to keep the paper-based BCP in a convenient place so that they can refer back to it as required.

The BCP will be supported by provision of facilities to encourage adherence. These will include personal supplies of moisturising cream for at-risk student nurses, and provision of (1) optimal equipment for cleaning hands, and (2) moisturising cream dispensers on ICUs.

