The BCP will be made available to ICU nurses once they have undergone baseline assessment (see below), and to student nurses 2 weeks before they start their first clinical attachment. It will be actively reinforced over the course of the study by consistent messages on skin care from the local OH and control of infection teams, and from local line management. Research has shown that senior role models have important effects on more junior healthcare workers’ hand hygiene behaviours [34, 35], and it seems reasonable to assume that this influence will extend to behaviours that prevent dermatitis. To facilitate this, when implementing intervention-plus, we will engage in a dialogue with local OH staff and line managers about the nature and purpose of the study and will provide them with information on the advice which will be given in the BCP, to ensure that they promote consistent messages on skin care. The SCIN research team will also write to any NHS sites at which student nurses undertake clinical placements, but which are not themselves participating study sites, to ensure they are informed about the study.

We will offer the BCP online to allow nurses to access it at a time convenient to their schedules, to permit standardisation of the delivery of key information across all intervention- plus sites, and to reduce the potential burden on OH staff. Moreover, if the BCP is found to be effective in this trial, it will be simple to scale up access to the website in order to deliver the BCP across the country.

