#### Study group 2 – intensive care nurses

ICU nurses who agree to participate will be asked to complete a self-administered baseline questionnaire (Questionnaire A) similar to that for student nurses, but also including items on current occupation; recent practices regarding use of gloves; recent practices regarding hand cleansing; recent use of moisturising creams; and any sickness absence or modification of duties during the past 12 months because of hand dermatitis. Arrangements for the return of completed questionnaires will be as for student nurses. They will also have their hands and wrists photographed.

Once recruitment has been completed, field workers at intervention-plus sites will promote the importance of optimising equipment for hand cleansing, and dispensation of moisturising cream. The written leaflet about prevention of hand dermatitis will be made available to all staff on the ward (not only those individuals who have consented to take part in the study), and an email will be sent via the lead ICU nurses to all staff on the ward with a link to the BCP. Uptake of the BCP will be documented.

Following recruitment, all ICU nurses (not just those who have agreed to participate in the study) at intervention-light sites will also be given the written leaflet about prevention of hand dermatitis.

Two weeks after the BCP has been offered (or at a similar interval after recruitment in the intervention-light sites), participants will be asked to complete a second questionnaire (Questionnaire B) about beliefs regarding prevention of dermatitis and (at intervention-plus sites) participation in, and views on the BCP. Questionnaire B will be sent to participants by post with a business reply envelope. All participants at both the intervention-plus and intervention-light sites will be encouraged (orally, through the written advice leaflet and by email reminders sent out by the SCIN research team at 4 and 8 months) to attend the OH department at an early stage should they develop hand dermatitis. Email reminders will also contain a positive reinforcement message to encourage ongoing participation in the study. In addition, at the intervention sites, the email reminders will reinforce the BCP.

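### The economic analysis costs only part of intervention-plus: ICU hand-cleaning equipment, dispensers and staff reinforcement have no explicit cost line

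*Protocol article*

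**What the plan says.** **What is costed.** In the protocol article, Economic analysis, healthcare costs have three parts. The first is clinical contacts, "based on the number of contacts with clinical staff (occupational health, primary care staff, dermatologists, etc.) as a result of hand dermatitis". The second is the supply of moisturising cream. The third is "the cost of the BCP itself, which will be based on development time and staff time accessing the package". Later the section notes that the intervention cost has to be worked out for this study and repeats the base: "This will be based on estimates of staff time spent developing the intervention and staff time spent accessing it". Both elements are then moved up and down by 10–50 % in sensitivity analyses, judged at £20,000 and £30,000 per QALY. If the intervention proves cost-effective, an NHS budget impact follows, with its uncertainty explored through the same sensitivity analyses.

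**What is delivered.** The Intervention-plus section includes "provision of (1) optimal equipment for cleaning hands, and (2) moisturising cream dispensers on ICUs" among the facilities that support the behavioural change programme (BCP). It describes the programme as "actively reinforced over the course of the study by consistent messages on skin care from the local OH and control of infection teams". Local line managers are to take part in this too. To make this happen, "we will engage in a dialogue with local OH staff and line managers about the nature and purpose of the study". Under Data collection, Study group 2, "field workers at intervention-plus sites will promote the importance of optimising equipment for hand cleansing" and the dispensing of cream.

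**What the comparator gets.** The Comparator section states that intervention-light nurses receive neither the programme nor its active reinforcement, and are not routinely offered cream beyond local standard practice.

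**The concern.** The effect estimate comes from the whole intervention-plus package, while the cost estimate comes from a subset of it. The uncosted items are described only for intervention-plus, so they do not cancel between the arms. The article does not leave the cost base to a later document. It names the base twice, and that base is narrower than the intervention it describes.

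Cost-effectiveness is a declared aim. The ICER per dermatitis-free participant, the cost-effectiveness acceptability curves and the budget impact all inherit the gap. The budget impact is the most exposed. Programme development is largely a one-off cost, whereas equipment, dispensers and staff time would be needed again at each adopting site.

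**Working it through.** The protocol states no intervention cost and no ICER, so there is no published figure to reproduce. The check has three steps.

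**1. Components against cost lines**

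| Intervention-plus component | Cost line in Economic analysis |
|---|---|
| BCP development | Yes |
| Staff time accessing the BCP | Yes |
| Moisturising cream | Yes |
| Cream dispensers on ICUs | None explicit; might be read into cream supply |
| Hand-cleaning equipment on ICUs | None |
| Reinforcement by OH, infection control and line managers | None |
| Briefing of OH staff and managers; field-worker promotion on ICUs | None; part may be research cost |

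The clinical-contact line does not pick up reinforcement, because it is limited to contacts caused by hand dermatitis. For student nurses the gap is reinforcement and briefing time only, since equipment and dispensers concern ICUs.

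**2. Effect on the ICER**

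Let c be the omitted cost per intervention-plus nurse (c ≥ 0), ΔC the incremental cost as counted, and Δp the absolute reduction in prevalence.

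- ICER as planned = ΔC / Δp
- ICER with all components = (ΔC + c) / Δp
- Understatement = c / Δp

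The Sample size section assumes 24 % prevalence at intervention-light sites and 10 %, 12 % or 14 % at intervention-plus sites, so Δp is 0.14, 0.12 or 0.10. The values of c below are assumptions chosen only to show the scaling.

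| Assumed c per nurse | Δp = 0.14 | Δp = 0.12 | Δp = 0.10 |
|---|---|---|---|
| £1 | £7.1 | £8.3 | £10.0 |
| £5 | £36 | £42 | £50 |
| £10 | £71 | £83 | £100 |
| £25 | £179 | £208 | £250 |
| £50 | £357 | £417 | £500 |

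For example, 10 / 0.14 = 71 and 10 / 0.10 = 100. The same formula with a QALY difference in the denominator gives the shift in cost per QALY. The protocol gives no planning value for that difference, so the shift cannot be computed.

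**3. Would the sensitivity analysis catch it?**

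Let K be the counted development plus access cost. Raising both elements by 50 % gives at most 1.5K. The cost with the omitted items is K + c. So the upper bound covers the omission only if K + c ≤ 1.5K, that is c ≤ 0.5K. If c is a quarter of K, the full cost is 1.25K and lies inside the range. If c equals K, it is 2K and lies outside. Nothing in the protocol says which case applies.

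**The case against.** Several objections have weight.

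- **Net direction.** The same costing charges programme development to the intervention. That is a one-off cost, and the Intervention-plus section says the website would be simple to scale up. Spread over trial participants alone, it raises the cost per nurse. This stands. A reader might infer that the ICER as a whole is biased in favour of intervention-plus, but the documents support a direction only for this one omission.
- **Size.** One could assume a spend per ICU and divide it by the trial nurses per site to obtain a pound figure. The protocol offers no unit cost to support this. The denominator would also be doubtful, because the leaflet and the programme link go to all ward staff and not only to those who consented. No such figure is defensible.
- **Decision relevance.** No effect on the conclusion at £20,000 or £30,000 per QALY can be shown. This stands too.
- **Sensitivity range.** It might be said that the planned range cannot reveal the gap. That goes too far: a small omission could fall within the +50 % bound, although nothing would identify it as such.
- **Equipment and dispensers.** One section speaks of providing equipment and another of promoting its optimisation, so who pays is unclear, and the incremental spend may be small where ICUs are already well equipped. The Comparator section does not expressly exclude equipment. Dispensers may belong to cream supply. Part of the dialogue with managers is research activity. These points narrow the amount without removing it, since a cost borne by the hospital counts from both of the stated perspectives.
- **Condensed article.** An itemised cost inventory could sit in a fuller document. That would excuse silence, but the article fixes a specific two-element base.

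**Conclusion.** The mismatch stands. As written, the plan measures the effect of the full package and costs part of it. Taken alone, this understates the incremental cost of intervention-plus by the omitted cost per nurse, and so lowers the ICER and the budget impact. At the protocol's own planning differences, each £1 omitted per nurse lowers the cost per extra dermatitis-free nurse by about £7 to £10.

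This rests on three assumptions: that the omitted items carry some cost at intervention-plus sites beyond what intervention-light sites spend, that intervention-plus has the better outcome, and that the risk difference is near the planning values. The absolute amount is unknown and may be small. Neither a net bias of the whole costing nor a changed decision at the QALY thresholds is established. The point concerns the economic aim and leaves the primary clinical analysis untouched. It should be corrected because the remedy is inexpensive.

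**What to change.** 1. Add to the intervention cost the incremental equipment, dispenser and installation costs at intervention-plus ICUs, taking care not to count dispensers twice if they are already within cream supply.
2. Add the time that OH, infection-control, line-management and field staff spend on reinforcement, leaving out time spent on research tasks.
3. Take these from a short cost log at each intervention-plus site, or from retrospective site estimates where the period has passed. The supply data listed under Outcome measures cover moisturiser requests and orders only, so equipment and dispensers need new collection.
4. Spread ward-level items over all exposed ward nurses, with trial nurses as the denominator in a sensitivity case.
5. Include the new items in the 10–50 % sensitivity analyses and in the budget impact.
6. State whether equipment is supplied or only promoted, so that the intervention and cost descriptions agree. If an item is left out, give the reason.

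The cost is a little extra data collection. Some of it would rely on recall, since the trial has been running since September 2014. The resulting ICER may be less favourable.
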